#### Clinical outcomes are secondary in this hybrid type III trial

Clinical outcomes reported are selected to assess the impact of improving adoption of guideline-concordant antimicrobial prophylaxis on important clinical outcomes theoretically linked to appropriate application of peri-operative prophylaxis, specifically, CIED infections (impacted by appropriate pre-procedural antimicrobial use), and AKI and *C. difficile infections* (both impacted by appropriate early discontinuation of antimicrobial use). These data will be extracted from the VA EHR using the automated algorithm and CIED infections will be validated by manual review at the main study site. Similar to the analysis of the implementation outcomes, incidence of key clinical outcomes will be measured pre- and post-implementation at each of the three sites, applying a generalized linear mixed model with allowance for a facility random effect. We will again explore the influence of calendar time in the stepped-wedge design using models described by Nickless et al. [35].

### Power calculations

#### Adoption of evidence-based practices (primary outcome)

Using the power estimation procedure of Hussey and Hughes [36], we will need to evaluate 135 cases from each site, inclusive of before and after the surveillance system is active, and setting alpha = 0.05, we will have 80% power to detect a difference in proportion greater than or equal to 0.15. In other words, if the rate of guideline discordant antimicrobial use in an individual facility changed from 50 out of 100 procedures to 35 out of 100 at each site after introduction of our audit and feedback system, we could detect a significant change in proportion. We assumed a coefficient of variation equal to 0.2 for this estimate. The three facilities perform >100 CIED procedures per year and all have rates of guideline discordant antimicrobial use following > 50% of procedures.

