##### Study design

A stepped-wedge implementation/effectiveness trial will be conducted at three VA medical centers.

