#### Impact on CIED infections outcomes (secondary)

Based on estimated incidence of CIED infections and *C. difficile*, and the number of procedures performed across the three facilities (*N*~2100), the study has 89% power to detect a doubling in the incidence of CIED infections (from 2 to 4%) and 50% power to detect a 50% reduction in infections (from 2 to 1%). These estimates were again derived from the formulas of Hussey and Hughes and assumed a coefficient of variation of 0.2 [36].

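### The 80% power for 135 cases per site holds only if calendar-period effects are left out of the Hussey and Hughes model; with them it is about 38–40% in a simple layout

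*Protocol article*

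**What the plan says.** The section on power for adoption of evidence-based practices names the Hussey and Hughes procedure and states "we will need to evaluate 135 cases from each site, inclusive of before and after the surveillance system is active", "setting alpha = 0.05", and "we will have 80% power to detect a difference in proportion greater than or equal to 0.15". The example is a discordant-use rate that "changed from 50 out of 100 procedures to 35 out of 100 at each site". On between-site variation it says "We assumed a coefficient of variation equal to 0.2 for this estimate". It does not say whether period effects were in the model, nor how many periods were assumed.

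Four other places bear on the figure:
- Trial design concedes that stepped-wedge trials are open to secular trends and justifies the design by its better control of them. Table 2 gives the schedule.
- Analysis of quantitative data elements first names an interrupted time-series analysis. It then describes a generalized linear mixed model comparing pre and post with a facility random effect, in which calendar time is only to be explored.
- Phase IV (data analysis) drops the wash-in period.
- The power section for CIED infections uses about 2,100 as the "number of procedures performed across the three facilities", which is about 700 per site.

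**The concern.** The cited procedure is the standard one for stepped-wedge trials, and its usual model has a fixed effect for each period. In a staggered roll-out, exposure and calendar time rise together, so adjusting for period removes much of the information on the treatment effect. With three sites the loss is large. A figure of 135 cases per site looks too small for a time-adjusted analysis of a 15-point change.

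If the figure assumes no secular trend without saying so, a reader will take 80% as the power of the design that was justified by trend control. A team that treated 135 per site as enough, and then adjusted for time, would more likely than not miss a true change from 50% to 35%.

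**Working it through.** **Inputs from the power section.** Rates 0.50 and 0.35 (difference 0.15); 135 cases per site in total; coefficient of variation 0.2; alpha 0.05. Three sites, from the Study design section: "A stepped-wedge implementation/effectiveness trial will be conducted at three VA medical centers".

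**Assumptions.** Two-sided test (z = 1.96). One site crosses at each of three steps, so four periods. Equal cells of 135/4 = 33.75 cases. Mean rate 0.425, so the cell variance is s = 0.425 × 0.575/33.75 = 0.007241. Site variance t = (0.2 × 0.50)² = 0.01. Power = Φ(0.15/SE − 1.96).

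**Design constants** (I = 3 sites, T = 4 periods). U = 3 + 2 + 1 = 6 exposed cells. W = 0² + 1² + 2² + 3² = 14 (squared column totals). V = 3² + 2² + 1² = 14 (squared row totals).

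**1. Reproducing the stated figure, without period effects.** With λ = t/(s + 4t) = 0.01/0.047241 = 0.21168, the information on the effect is

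(U − λV)/s − (U²/12)/(s + 4t) = (6 − 2.9635)/0.007241 − 3/0.047241 = 419.4 − 63.5 = 355.9.

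SE = 0.0530 and power = Φ(2.83 − 1.96) = 80.8%. With the variance taken at the baseline rate (0.25/33.75), SE = 0.0536 and power = 79.9%. Solving for 80% gives 133 and 136 cases per site. The stated 135 and 80% are recovered.

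**2. The same inputs with period effects (Hussey and Hughes closed form).**

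Var = I·s·(s + T·t) / [(IU − W)·s + (U² + ITU − TW − IV)·t]

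= 3 × 0.007241 × 0.047241 / [(18 − 14) × 0.007241 + (36 + 72 − 56 − 42) × 0.01] = 0.001026/0.12896 = 0.00796.

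SE = 0.0892 and power = Φ(1.68 − 1.96) = 39.0%. Baseline-rate variance gives SE 0.0901 and 38.4%. Site SD 0.2 × 0.425 gives SE 0.0881 and 39.9%. The detectable difference at 80% power is (1.96 + 0.84) × 0.0892, about 25 points. For 80% power at 15 points, about 391–405 cases per site are needed.

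**3. Can another reading rescue 80% with period effects?** At 135 per site in total, no:

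| Variant | Power |
|---|---|
| One-sided alpha 0.05 | about 51% |
| Coefficient of variation 0 | 53% |
| Coefficient of variation 0.5 | 37% |
| 5 to 7 periods | 28–35% |
| Best unequal allocation found, 4 periods | about 57% |

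Reading the figure as 135 before plus 135 after gives 56%. Only 135 per site and period passes 80% (about 90%), and the wording that counts before and after together excludes it.

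**4. Supporting check.** In the same layout with about 2,100 procedures, the 89% quoted for a rise in CIED infections from 2% to 4% is approached without period effects (88.7%, variance at 2%) and not with them (53%). The companion 50% figure did not reproduce either way, so this check carries little weight.

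**5. Table 2 schedule, period effects included.** Layout in quarters to month 36, with the column printed as 30–46 read as ending where the analysis phase begins. Cases are spread evenly over the analysed time at each site.

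| Start of exposure, and exclusions | 135 per site | 700 per site |
|---|---|---|
| Reports; wash-in excluded; education and adaptation count as control | 11% | 37% |
| Reports; nothing excluded | 20% | 71% |
| Education; nothing excluded | 26% | 84% |
| Education; wash-in excluded | 27–28% | 86% |
| Reports; education, adaptation and wash-in all excluded | not estimable | not estimable |

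The last row fails because no period then contains both exposed and unexposed sites. If the 700 include wash-in procedures that are later dropped, the first row falls to about 34–35% and the fourth to about 82–83%. In the simple four-period layout, 700 per site gives about 96%.

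**The case against.** The strongest reply is that nothing was miscalculated. The 80% reproduces, and it matches the mixed model in the analysis section: pre against post, a facility random effect, calendar time only explored. Under that model the power section and the analysis section agree. This stands, and it rules out calling the figure an arithmetic slip. It does not settle the matter, because the same section also names an interrupted time-series analysis, which models time, and the design was chosen for its control of trends. Nor does the text tell the reader that 80% assumes no trend.

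A second reply is that 135 is a minimum, well below the procedures available. This also stands. A reader might infer that 135 per site contradicts the roughly 2,100 procedures in the next section. It does not: one is a requirement for a common outcome, the other a count of available procedures applied to a rare one. Nothing says that only 135 per site will be analysed.

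A third reply is that any single Table 2 figure depends on a choice the text leaves open. The lowest figures count education and adaptation as control time, although education is part of the intervention bundle. That is why a range is given here. Finally, the limitations section already admits that the non-randomised design weakens causal attribution. That is candid, but it does not disclose the assumption behind the power figure.

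**Conclusion.** The point holds in a limited form. The statement of 135 cases per site and 80% power is valid only for an analysis without calendar-period effects. With them, power is about 38–40% in a three-site, four-period layout with equal cells, and about 390–405 cases per site would be needed. That layout is an assumption, and a favourable one: the estimable Table 2 layouts give about 11–28% at 135 per site.

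A reader might go further and conclude that the trial is underpowered. The document does not support that. At about 700 procedures per site, time-adjusted power is about 96% in the simple layout and about 37–86% on Table 2, according to the start of exposure and the exclusions. What is shown is that 135 is unsafe as a target and that the stated power does not match the rationale for the design. All figures assume the stated coefficient of variation of 0.2, an immediate and constant effect, and a normal-approximation test.

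**What to change.** In the power section for the primary outcome:
- Withdraw the figure of 135 per site with 80% power, or label it as assuming no secular trend.
- State that all eligible procedures (about 2,100) enter the primary analysis.
- Restate the power, or the detectable difference, from a time-adjusted model on the Table 2 schedule. Give the start of exposure, the excluded periods, the cell sizes and the coefficient of variation.

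The start of exposure and the exclusions need to be settled first, because one combination leaves the effect inestimable and the others move power at 700 per site from about 37% to about 86%.

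The cost is a recalculation and probably a less favourable stated figure. No extra patients are needed, because the roughly 2,100 procedures are already expected at the three sites.

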#### Impact on CIED infections outcomes (secondary)

Based on estimated incidence of CIED infections and *C. difficile*, and the number of procedures performed across the three facilities (*N*~2100), the study has 89% power to detect a doubling in the incidence of CIED infections (from 2 to 4%) and 50% power to detect a 50% reduction in infections (from 2 to 1%). These estimates were again derived from the formulas of Hussey and Hughes and assumed a coefficient of variation of 0.2 [36].

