#### Quality monitoring/audit and feedback reports

Reports created by the primary site will be provided to local champions (i.e., infectious diseases/infection control team members) via a secured data transfer method. Reports will include data such as (1) rates of appropriate pre-procedural antimicrobial use, (2) CIED infection events and rates, (3) antimicrobial-associated adverse events and rates (e.g., *C. difficile* infections, AKIs), (4) rates of post-procedural antimicrobial use benchmarked to high-performing facilities and providers, and (5) CIED infection rates benchmarked to other facilities. Rates of guideline-concordant antimicrobial use are included to reinforce positive behavior (learning), and rates of guideline-discordant use and benchmarking are included to promote unlearning and de-adoption. The reports will give the sites information about application of guideline-concordant practices at other high-performing facilities to ensure providers that they are not “outliers,” a barrier identified in formative evaluations. Rates of infections and adverse events are included to provide reassurance that the practice change is improving clinical outcomes by reducing non-cardiac adverse events and not worsening CIED infection rates. Adverse events that arise from inappropriate antimicrobial use are included to highlight tangible harms associated with lack of guideline compliance and to promote *unlearning*.

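### The stated 89% power for a doubling of CIED infections is too high for about 2100 procedures: about 75% for the analysis described, and it does not share its assumptions with the 50% printed beside it

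*Protocol article*

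**What the plan says.** The section Impact on CIED infections outcomes (secondary) gives two power figures. For a rise it claims that "the study has 89% power to detect a doubling in the incidence of CIED infections (from 2 to 4"%). For a fall, the same sentence goes on to claim "50% power to detect a 50% reduction in infections (from 2 to 1"%). The basis is "the number of procedures performed across the three facilities (*N*~2100"). On method it says "These estimates were again derived from the formulas of Hussey and Hughes", and it "assumed a coefficient of variation of 0.2". Alpha appears only in the primary-outcome power section ("setting alpha = 0.05"), without sidedness. The number of periods, the binomial variance entered and whether period effects were included are not given.

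The analysis of clinical outcomes (section Clinical outcomes are secondary in this hybrid type III trial) is a pre/post generalized linear mixed model with a facility random effect. Calendar time is to be explored, not fitted in the main model. Under Quality monitoring/audit and feedback reports, infection rates are fed back to sites partly as reassurance that the change in practice is "not worsening CIED infection rates".

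**The concern.** At a fixed sample size, a stepped-wedge analysis with a site random effect should not have more power than an unclustered comparison of the same procedures split evenly or at the best ratio. A quick two-group check of 2% against 4% with 2100 procedures gives well under 89%, so the figure looked wrong before any stepped-wedge detail came in. The companion figure did not fit either: settings that give 89% for the rise do not give 50% for the fall.

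The section on the conceptual model lists, among the barriers, clinicians' concern that stopping antimicrobials might raise device infections. A reader who sees 89% will suppose that a true doubling would be missed about one time in nine (11%). At 75% it would be missed about one time in four.

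**Working it through.** **Inputs.** From the article: N about 2100, three sites, rates 2% to 4% and 2% to 1%, coefficient of variation 0.2, alpha 0.05, Hussey-Hughes. Assumed: two-sided test; four equal periods with one site crossing over at each step; equal site volumes. This gives 2100/(3 × 4) = 175 procedures per site-period, between-site SD τ = 0.2 × 0.02 = 0.004 and τ² = 0.000016.

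**Formula without time effects.** Let s² be the binomial variance divided by 175, and c = τ²/(s² + 4τ²). In this layout 6 of 12 cells are intervention cells, and the sum over sites of squared intervention periods is 9 + 4 + 1 = 14. Then

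Var = s² / [6 − 14c − (36/12)(1 − 4c)] = s² / (3 − 2c), and power = Φ(|difference|/SE − 1.96).

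**1. Reproducing the plan's figure.** Use the 2% variance in both conditions: 0.02 × 0.98 = 0.0196.

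- s² = 0.0196/175 = 0.000112; c = 0.000016/0.000176 = 0.0909; SE = √(0.000112/2.818) = 0.00630.
- 2% to 4%: 0.02/0.00630 = 3.17, power **88.7%** (stated 89%).
- 2% to 1%: 0.01/0.00630 = 1.59, power **35.4%** (stated 50%).
- Primary outcome, same recipe: 405 cases, 33.75 per cell, variance 0.25, τ = 0.1. SE = 0.0536, 0.15/0.0536 = 2.80, power **79.9%** (stated 80%).

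This is probably how the 89% and the 80% were obtained. A one-sided test does not reconcile the pair: the same setting then gives 93.7% and 47.7%.

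**2. Variance reflecting both rates, no time effects.**

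- 2% to 4%: variance at the mean rate 0.03 × 0.97 = 0.0291; s² = 0.000166; c = 0.0695; SE = 0.00762; ratio 2.62; power **74.6%** (74.8% with each cell given its own variance).
- 2% to 1%: 0.015 × 0.985 = 0.01478; s² = 0.0000844; c = 0.108; SE = 0.00551; ratio 1.82; power **44.3%** (44.4% with cell-specific variance).

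At 50% against 35% the shortcut is harmless (79.9% against 81.7% with cell-specific variance). At 2% against 4% it adds about 14 points, because 0.04 × 0.96 = 0.0384 is nearly twice 0.0196.

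**3. Plain two-group check, 1050 against 1050, no clustering.**

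- 2% to 4%: SE = √[(0.0196 + 0.0384)/1050] = 0.00743; ratio 2.69; power **76.8%**. The best split, about 42:58, gives 77.9%. One-sided, the best is about 86%.
- 2% to 1%: SE = √[(0.0196 + 0.0099)/1050] = 0.00530; ratio 1.89; power **47.1%**.

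**4. With period effects in the model** (same layout). Var = 3s²(s² + 4τ²)/(4s² + 10τ²).

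- 2% to 4%, variance 0.0291: SE = 0.0118; power **39.6%** (52.7% with the 2% variance).
- 2% to 1%, variance 0.01478: SE = 0.00869; power **20.9%**.

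| Setting (two-sided, N = 2100) | 2% to 4% | 2% to 1% |
|---|---|---|
| Stated | 89% | 50% |
| 2% variance throughout, no time effects | 88.7% | 35.4% |
| Both rates' variance, no time effects | 75% | 44% |
| Plain two-group, both variances | 77% | 47% |
| Both rates' variance, period effects | 40% | 21% |

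No row gives the stated pair. With the variance at both rates and no time effects, about 3,130 to 3,150 procedures would be needed for 89%.

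**The case against.** Four points can be made for the plan.

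- *The 89% is traceable.* It follows from a recognisable simplification that also yields the primary figure, and with that variance even the plain two-group test gives 90.5%. This stands as an explanation, so 89% should not be called inexplicable. It does not make the figure right, since the outcome variance at 4% is not the variance at 2%.
- *The 50% is nearly right.* For the analysis described, 44 to 47% is close. This stands. The fault in that figure is mainly that it cannot come from the same two-sided setting as the 89%.
- *The 40% is not a property of this trial.* A reader might infer that the true power is 40%. The article does not support this: the value needs four equal periods and calendar time in the main model, and neither is stated. Layouts drawn from Table 2 give about 9 to 23% with period effects, so 40% is one point in a wide range. It belongs beside the corrected figure, not in its place.
- *The outcome is secondary, and the article nowhere says that a non-significant test will be read as safety.* This stands too. The phrase about infection rates not worsening explains why they are in the feedback reports; it is not a rule of inference.

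Two further inferences are not supported. Placing the whole rise on 15 switching procedures per 100 treats the minimum detectable change as the expected one. Rebuilding N from 100 procedures per site-year treats a selection threshold as the expected volume, when about 2100 is stated directly.

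**Conclusion.** Wrong as written; should-fix, on a secondary outcome. For the described analysis the power to detect a doubling is overstated by about 12 to 14 points: 89% against 75 to 77%. The chance of missing a doubling is therefore about 23 to 25%, not 11%. The two printed figures also cannot come from one set of two-sided assumptions.

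The 75% assumes three equal sites, four equal periods, τ = 0.004 and no time effects. The 77% needs no layout assumption beyond an even split, and no split exceeds 78%. The conclusion that 89% is too high does not depend on period effects. With them, power is much lower, by an amount that depends on a layout the article does not fix. The primary sample size does not rest on this calculation.

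**What to change.** - Recompute both figures with the variance at each rate. For the analysis described, replace 89% with about 75% and 50% with about 44 to 47%.
- Alongside, give the power with calendar time in the model (about 40% and 21% if four equal periods are assumed). The Trial design section justifies the stepped wedge by its control of secular trends, so readers will want this figure.
- State the periods, the sidedness and whether time effects are included.
- Say that the infection result will be interpreted through the difference and its 95% CI, and that a non-significant test will not be taken as evidence that infections did not rise.

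The cost is one recalculation and a few sentences. The stated power becomes less favourable; recruitment, design and the primary sample size do not change.

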#### Qualitative Data Collection and Analysis

Qualitative data will be collected through semi-structured interviews with key stakeholders using interview guides developed using the iPARIHS framework. Interview guides will contain questions related to feasibility, acceptability, and future adaptations to ensure that important implementation outcomes are represented.

Summative evaluations at each of the study sites will elicit electrophysiology team members’ perspectives about how reports impacted clinical practice decisions. Interviews with electrophysiologists will explore whether the information supplied in the reports was acceptable and useful and whether reports lead to practice change. Electrophysiologists will also be asked which elements of the multi-faceted implementation strategy impacted their practice the most, how the audit and feedback contributed to change (e.g., unlearning), and about fidelity to guidelines. Data from interviews with infectious diseases and infection control team members will focus on feasibility, and adaptations and will be analyzed separately. Infection control and antimicrobial stewardship specialists will be asked about any changes to local processes, protocols, or procedures that may have resulted from the implementation strategy and for input regarding which elements of the strategy they found to be the most useful (acceptability), and for any suggestions for how to improve it for future adaptation and dissemination. If changes to local policies were made, investigators will request protocol documents from before and after the change and they will be compared and classified according to the type of change (e.g., new EHR order set, new facility policy, etc.). If a facility demonstrates limited or no positive change, semi-structured interviews will explore why electrophysiology teams found the strategy to be ineffective and potential future adaptations will be identified. If there is differential effectiveness across sites, facilities with high levels of de-implementation will be compared to facilities with low levels of de-implementation to identify potential factors that may have impacted success, including acceptability, feasibility, and cost factors. Information about how the reports impacted clinical care, including information about unintended consequences, will be collected.

